##### Surgical Site Infection Cases

SSI cases will be identified through EHR review in conjunction with microbiological data. The data recorded is shown in Textbox 3.

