##### Detection of
*S. aureus* Surgical Site Infection

As a first step, we will export the data listed in the Data Collection Cohort section from all patients who underwent surgery in each center in 2016. We expect a minimum of 100,000 cases to be included in the cohort. *S. aureus* SSI that occurred in 2016 will be detected using microbiological data. 

To ensure feasibility, only centers with the capability of electronic microbiologic data export will participate. All patients presenting a *S. aureus* infection from the following will be identified: (1) wound swabs, (2) aspirates, (3) samples obtained during surgery, and (4) blood cultures.

Subsequently, electronic matching with clinical data will be performed in order to determine those patients who underwent a surgical procedure and had an *S. aureus* infection. This approach provides a sensitivity of 100% for identification of proven *S. aureus* SSI cases.

Data collected for surgical site infection cases.Length of hospitalizationLength of intensive care unit (ICU) stayReason for ICU stay; attribution to surgical site infections (SSI)Hours of mechanical ventilationHemodialysisSurvival at 30 and 90 daysIn case of death, attribution to SSINecessity for revision surgeryIn case of SSI, attribution to SSINecessity for readmissionIn case of readmission:ReasonAttribution to SSILength of hospitalizationLength of ICU stayHours of mechanical ventilationAll antibiotic treatments, including duration and dosageAll antibiotic treatments, including durationFunctional status at admission and at final dischargeCausative pathogens including resistance patternsType of SSI according to European Centre for Disease Prevention and Control criteria

All patients identified will be documented manually. Occurrences of SSI will be verified on a case-by-case following the criteria of the Hospital Acquired (HAI) SSI protocol [1].

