###### Superficial Incisional

Infection occurs within 30 days after the operation and involves only skin and subcutaneous tissue of the incision and at least 1 of the following: (1) purulent drainage with or without laboratory confirmation, from the superficial incision; (2) organisms isolated from an aseptically obtained culture of fluid or tissue from the superficial incision; (3) at least 1 sign or symptom of infection (pain or tenderness, localized swelling, redness, or heat and superficial incision is deliberately opened by surgeon, unless incision is culture-negative); and (4) diagnosis of superficial incisional SSI made by a surgeon or attending physician.

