###### Organ Space

Infection occurs within 30 days after the operation if no implant is left in place or within 1 year if the implant is in place and the infection appears to be related to the operation and infection involves any part of the anatomy (eg, organs and spaces) other than the incision that was opened or manipulated during an operation and at least 1 of the following: (1) purulent drainage from a drain that is placed through a stab wound into the organ/space; (2) organisms isolated from an aseptically obtained culture of fluid or tissue in the organ/space; (3) an abscess or other evidence of infection involving the organ/space that is found on direct examination, during reoperation, or by histopathologic or radiologic examination; or (4) diagnosis of organ/space SSI made by a surgeon or attending physician.

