With SSI rates being the primary endpoint, SSI detection methodology is crucial in this study. Prior studies and surveillance effort, if specifying detection methodology at all, are usually limited to the analysis of administrative code data [14,15]. However, a recent publication demonstrated that using bacteriological data is superior and combining both—administrative and bacteriological data—could be even more advantageous [16]. In this very study, the detection by means of bacteriologic data will result in high sensitivity, specificity, and negative predictive values (96.4%, 91.4%, and 99.9%, respectively) for deep SSI with no significant difference to the use of both types of data.

Cases are matched 1:1 to controls within each center by software provided by the coordinating center. Matching cases and controls within centers addresses the need for risk-adjustment to institutional characteristics and practices. Cases are matched to controls that received the same type of procedure. Individual pair-wise matching will be used, utilizing optimal matching to ensure the overall smallest possible Euclidean distance between cases and controls. Acknowledging the limited utility of using the National Healthcare Safety Network (NHSN) risk index, which only accounts for the existence of certain risk factors but not their composition, a propensity score is determined by logistic regression.

Costs are calculated by multiplication of the per-unit price for major cost drivers with the number of units used. Minor cost drivers, such as drug use, will be disregarded, as length of stay has been repeatedly shown to account for 90% of excess SSI costs [11].

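### The specimen list that triggers case review does not name drain fluid or tissue taken outside surgery, so the stated 100% sensitivity for proven S. aureus SSI is unsupported and incidence may be biased downward

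*Protocol article*

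**What the plan says.** Under Detection of S. aureus Surgical Site Infection, cases are detected from microbiological data. Patients are picked out when S. aureus is found in one of four specimen groups: "1) wound swabs, (2) aspirates, (3) samples obtained during surgery, and (4) blood cultures". These results are linked electronically to the surgical records. Then "All patients identified will be documented manually", and each SSI is checked against the HAI-SSI criteria. On performance, the section states: "This approach provides a sensitivity of 100% for identification of proven" S. aureus SSI.

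The criteria used for that check include two culture items. Superficial criterion 2 is "organisms isolated from an aseptically obtained culture of fluid or tissue from the superficial incision". Organ/space criterion 2 is "organisms isolated from an aseptically obtained culture of fluid or tissue in the organ/space". Organ/space criterion 1 is "purulent drainage from a drain that is placed through a stab wound into the organ/space".

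Two other places bear on the point. The section Surgical Site Infection Cases says more generally that "SSI cases will be identified through EHR review in conjunction with microbiological data". Principal Findings, in the Discussion, reports for detection by bacteriological data "high sensitivity, specificity, and negative predictive values (96.4%, 91.4%, and 99.9%, respectively) for deep SSI". The Limitations section of the Discussion names one source of missed cases, infections arising after discharge.

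**The concern.** The screen comes first and verification second. Verification can remove a patient who was flagged wrongly, but it cannot recover one who was never flagged. The screen must therefore be at least as wide as the definitions it serves, and on its wording it is narrower. Drain fluid, and tissue taken on the ward or at a bedside procedure, are not named, although the two culture criteria accept fluid or tissue without asking where it was taken.

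The primary objectives are the overall and procedure-specific incidence of S. aureus SSI, and rates and costs are also to be reported by depth of infection. A gap in the screen lowers the numerator in one direction only. It is likely to fall mostly on organ/space infections, where drain fluid is a natural sample. A larger cohort does not reduce it. It is also separate from post-discharge loss, because the missed result is already in the hospital's own laboratory data.

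**Working it through.** **1. Specimen list against culture criteria**

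| Specimen positive for S. aureus | Accepted by a culture criterion? | Named in the screening list? |
|---|---|---|
| Wound swab | not decisive here | yes |
| Aspirated collection | yes (fluid) | yes |
| Tissue or fluid from operation or reoperation | yes | yes |
| Blood culture | not decisive here | yes |
| Drain fluid, organ/space, aseptically obtained | yes (organ/space criterion 2) | no, unless filed as an aspirate |
| Tissue taken outside surgery, superficial or organ/space | yes (superficial 2, organ/space 2) | no |

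The list carries no wording such as 'for example', so it reads as closed. The gap is the last two rows, and only for patients with no positive result in a listed specimen. The Deep Incisional criteria contain no culture item of this kind, so the gap does not arise there from the definitions.

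**2. The protocol's own figures**

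- Expected cases (Sample Size): 150,000 × 0.015 = 2250. Reproduced.
- Precision (Sample Size): 1.96 × √(0.01 × 0.99 / 1500) = 0.504 percentage points, against the stated 0.5. Reproduced.

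Neither figure depends on the specimen list.

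**3. What imperfect sensitivity would do**

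With true incidence 1.5%, N = 150,000 and sensitivity s, observed incidence = 1.5% × s and missed cases = 2250 × (1 − s).

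| s | Observed incidence | Missed of 2250 |
|---|---|---|
| 99% | 1.485% | 22.5 |
| 98% | 1.470% | 45 |
| 96.4% | 1.446% | 81 |
| 95% | 1.425% | 112.5 |
| 92.5% | 1.388% | 169 |
| 90% | 1.350% | 225 |

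The 96.4% row borrows the Discussion's figure for deep SSI as an illustration only.

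The 98% and 92.5% rows match one assumed scenario: 20% to 30% of cases are organ/space, and 10% to 25% of those are proven only from an unlisted specimen. Then 0.20 × 0.10 = 2.0% and 0.30 × 0.25 = 7.5% of all cases are lost. Neither share is in the documents.

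**4. Compared with sampling error**

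- Overall rate: half-width 1.96 × √(0.015 × 0.985 / 150,000) = 0.062 points, or 4.1% of the rate. The scenario's shift is 1.5 × 0.02 = 0.03 to 1.5 × 0.075 = 0.11 points, so it passes sampling error once about 4% of cases are lost.
- Organ/space rate, lower end: 0.20 × 1.5% = 0.30%; half-width 1.96 × √(0.003 × 0.997 / 150,000) = 0.028 points; shift 0.10 × 0.30 = 0.03 points.
- Organ/space rate, upper end: 0.30 × 1.5% = 0.45%; half-width 1.96 × √(0.0045 × 0.9955 / 150,000) = 0.034 points; shift 0.25 × 0.45 = 0.11 points.
- One procedure with 1500 operations: half-width about 0.5 points, so an average loss of this size is well inside sampling error.

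**5. Effect on the control pool**

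At the upper end, apparent non-cases number 150,000 − 2250 + 169 = 147,919. Missed cases among them are 169 / 147,919 = 0.11%, or about 3 of 2250 controls if drawn at random.

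**The case against.** The best defence is that the four headings are summary groups. Aspirates is a broad term, some laboratories may file drain fluid there, and the mapping of specimen codes may sit in a full protocol or export manual that is not shown. This partly stands: the real loss could be close to zero. But the article itself fixes the list and the 100%. If centers read the headings differently, they apply different filters, which matters because rates are to be compared by institution and country.

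A second defence is that other routes exist. Surgical Site Infection Cases mentions record review together with microbiology, and item 8 of the Cohort data list exports SSI occurrence within 90 days. Neither is set out as a parallel way of finding S. aureus cases. The detection section makes microbiology the entry step, and the Cohort list is described as descriptive only.

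Third, a patient with pus from a drain but no culture is not a proven S. aureus SSI, so organ/space criterion 1 does not by itself contradict the 100%. That stands; the point rests on the two culture criteria. Likewise, 96.4% concerns deep SSI and is not a direct estimate for proven S. aureus cases. It sits badly with 100% but does not supply the true value.

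A reader might infer that organ/space infections never reach chart review. The documents do not support that: any positive wound swab, aspirate, operative or reoperative sample, or blood culture flags the patient. Nor is the control pool materially contaminated, as step 5 of the working shows.

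**Conclusion.** The mismatch holds as a matter of text. The list omits two specimen sources that the superficial and organ/space culture criteria accept, and no other case-finding route is set out. Followed literally, patients positive only in those specimens are missed, so the 100% sensitivity statement has no support.

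The direction of any bias is downward and it would fall mainly on organ/space rates. Its size cannot be derived from the documents. The 45 to 169 missed cases (incidence 1.47% to 1.39% instead of 1.5%) rest wholly on assumed shares. If those shares were right, the organ/space rate would be affected more clearly than the overall rate, and the rate for a single procedure of 1500 operations would show little beyond sampling error. This merits a correction to the screening rule; it does not overturn the design.

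**What to change.** In Detection of S. aureus Surgical Site Infection, add drain fluid and tissue or biopsy cultures from the surgical site, wherever taken, to the specimen list. Apply the same list, with the same reading of aspirates, at every center. Let the case-by-case verification already planned reject patients without an SSI. Remove the 100% sensitivity statement, or justify it and reconcile it with the 96.4% in Principal Findings.

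The cost is a wider filter in an electronic export that already exists, plus some additional charts reviewed and rejected. Centers that have already run the export would need to rerun it. Screening every S. aureus-positive clinical specimen would also close the gap, but it would bring in isolates unrelated to the surgical site and is not needed for this point.

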### Limitations

A limitation of this study is the inability to detect late infections occurring post discharge by only analyzing in-patient laboratory data for SSI case identification. Depending on the procedure in question, infections occurring after discharge constitute a notable percentage of SSI. A post discharge surveillance approach will be subject of a future sub study.

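### The stated 100% sensitivity covers only positive cultures already in the centre's exported laboratory data, yet the primary endpoint is the unrestricted, procedure-specific incidence of S. aureus SSI

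*Protocol article*

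**What the plan says.** The Methods section on detecting S. aureus SSI builds case finding on laboratory exports. Of S. aureus infections it says: "SSI that occurred in 2016 will be detected using microbiological data". The isolates are linked electronically to patients operated on in 2016, and the plan concludes: "This approach provides a sensitivity of 100% for identification of proven" S. aureus SSI. Flagged patients are then documented by hand: "Occurrences of SSI will be verified on a case-by-case following the criteria" of the HAI SSI protocol.

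Other parts of the article bear on this:

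- **Discussion, Limitations** concedes an "inability to detect late infections occurring post discharge by only analyzing in-patient laboratory data for SSI case identification" and adds: "Depending on the procedure in question, infections occurring after discharge constitute a notable percentage of SSI". Post-discharge surveillance is left to a later sub-study.
- **Deep Incisional** and **Organ Space** accept infections up to 1 year after surgery when an implant is in place, and 30 days otherwise. The **Cohort** variable list records SSI within 90 days.
- **Primary Objectives** and **Primary Analysis** define the target as the overall and procedure-specific incidence of S. aureus SSI in Europe, with 95% CIs. Neither restricts it by culture, place of detection or date of onset.
- **Introduction, Background** says the authors want to show that the S. aureus SSI rate does not vary with the procedure.

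**The concern.** The 100% is close to true by construction: a patient with a positive culture in the export will be found in the export. It is not true of every proven case. An S. aureus SSI cultured outside the centre's in-patient laboratory data is proven but not found. So is one cultured at the centre in early 2017 after an operation in late 2016.

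The first loss varies by procedure, as the Limitations section itself says. The second falls hardest on implant procedures, whose window is longest. The planned binomial CI reflects sampling error only and shows neither.

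What is at stake is the procedure comparison. If capture differs between procedures, a true common rate can look heterogeneous and true differences can look flat. A reader who takes the 100% at face value has no reason to suspect either.

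**Working it through.** **1. The plan's own figures.** Wald precision, n = z²p(1−p)/d², with p = 1% and d = 0.5 points:

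- n = 3.8415 × 0.0099 / 0.000025 = 1521, against the stated 1500 (half-width at 1500: 0.504 points). Reproduced.
- Expected cases: 0.015 × 150,000 = 2250. Reproduced.
- The 100% has no stated inputs and cannot be derived.

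**2. Sampling error of the overall rate.** At p = 1.5% and N = 150,000: 1.96 × √(0.015 × 0.985 / 150,000) = 0.062 points.

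**3. Effect of missed infections.** Reported rate = true rate × (1 − f), where f is the share not visible in the centre's laboratory data. The documents do not give f; 10% to 50% is assumed. With a true rate of 1.5% and N = 150,000:

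| f (assumed) | Reported rate | Cases missed | Shift (points) | Shift ÷ half-width at reported rate |
|---|---|---|---|---|
| 10% | 1.35% | 225 | 0.15 | 2.6 |
| 30% | 1.05% | 675 | 0.45 | 8.7 |
| 50% | 0.75% | 1125 | 0.75 | 17.2 |

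**4. Effect on the procedure comparison.**

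- *Creating a difference:* two procedures, both truly at 1.5%, with f = 10% and 50%, are reported as 1.5 × 0.9 = 1.35% and 1.5 × 0.5 = 0.75%.
- *Hiding one:* a procedure truly at 2.7% with f = 50% is reported as 2.7 × 0.5 = 1.35%, the same as one truly at 1.5% with f = 10%.

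The spurious gap is 0.60 points. With 1500 operations in each procedure, the 95% half-width of the difference is 1.96 × √((0.0135 × 0.9865 + 0.0075 × 0.9925) / 1500) = 0.73 points, so the gap would not stand out. It equals the half-width at n = 3.8415 × 0.02076 / 0.006² ≈ 2,200 per procedure. For larger procedures, a difference in capture alone would tend to look like a real difference.

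**5. The 2016 restriction.** If operations are spread evenly over 2016, an infection with onset d days after surgery falls in 2017 with probability d/366. That is 2.7% at 10 days, 8.2% at 30 days and 24.6% at 90 days. It rises further for implant infections later in the 1-year window.

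**The case against.** Several points on the other side stand.

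- **The claim is qualified.** Methods limits the 100% to proven cases. It should not be read as a claim about all S. aureus SSI. Even so, the Limitations section and the 2016 restriction show that some proven cases are lost.
- **The limitation is disclosed.** It is, in the Discussion. But the Methods statement, the objectives and the primary analysis are not aligned with it.
- **Readmissions are recorded.** An infection cultured on readmission to the same centre can be found, so not every post-discharge infection is lost.
- **A sensitivity analysis may be left to the SAP.** Its absence here is not the point; it is part of the remedy.
- **The data years can be widened.** Target Population allows data from 2015 to 2017, but only if too few data are available. That is not a follow-up rule for operations in 2016.

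Stronger readings are tempting, but the documents do not support them:

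- *That the quoted sensitivity contradicts the 100%.* Principal Findings gives "96.4%, 91.4%, and 99.9%, respectively) for deep SSI", a figure not specific to S. aureus, and it is unclear whether it belongs to the cited publication or to this study. Applied anyway, it moves 1.5% only to 1.5 × 0.964 = 1.446%, about 0.9 half-widths.
- *That SSI diagnosed without culture is a measurable loss.* The superficial criteria do accept "purulent drainage with or without laboratory confirmation, from the superficial incision". In this design, however, the criteria verify patients already flagged by an isolate, and the documents offer no way to attribute an uncultured SSI to S. aureus.
- *That the reported rate is a lower bound for Europe.* Centres are selected (more than 10,000 surgeries), which can move the rate either way.
- *That capture falls with shorter stay by a known amount.* This is plausible, but the documents give no capture by length of stay.

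**Conclusion.** The concern holds in limited form. The 100% describes completeness within the exported laboratory data and detection window, not sensitivity for proven S. aureus SSI. The primary endpoint is worded more broadly than what is measured, and the article itself says that part of the loss varies by procedure. That leaves the aim of showing a procedure-independent rate exposed to a bias that the CIs do not show.

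The size is not known. The 1.35% versus 0.75% contrast and the shifts of 2.6 to 17 half-widths rest on assumed missed shares of 10% to 50%. The large multiples apply to the overall rate; at about 1500 operations per procedure, sampling error is of similar size to the bias. The direction, under-ascertainment within the participating centres, assumes that case-by-case verification removes false positives. With the quoted specificity of 91.4%, that matters: at 1.5%, the positive predictive value before verification would be 0.964 × 0.015 / (0.964 × 0.015 + 0.086 × 0.985) = 14.6%.

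**What to change.** 1. Restate the 100% as completeness for culture-positive cases in the participating centre's own laboratory data within the detection window.
2. Reconcile the 2016 onset restriction with the 90-day window in the Cohort list and the 30-day and 1-year windows in the case definitions, so that every operation has a defined period at risk.
3. Name the primary endpoint as culture-proven S. aureus SSI detected at the participating centre, including on readmission. State in the objectives and primary analysis that it under-ascertains all S. aureus SSI within those centres.
4. Before concluding that rates do or do not depend on procedure, divide the procedure-specific rates by a range of assumed capture fractions, allowed to differ between procedures. In the example above, 1.35 / 0.9 and 0.75 / 0.5 both return 1.5%.
5. Use the SSI field in the cohort export as a cross-check only. It is not limited to S. aureus and may itself miss post-discharge cases, so it is not an upper bound. Stratification by depth is already planned and needs no change.

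The cost is a narrower headline claim and a little more analysis, with no new data.

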###### Superficial Incisional

Infection occurs within 30 days after the operation and involves only skin and subcutaneous tissue of the incision and at least 1 of the following: (1) purulent drainage with or without laboratory confirmation, from the superficial incision; (2) organisms isolated from an aseptically obtained culture of fluid or tissue from the superficial incision; (3) at least 1 sign or symptom of infection (pain or tenderness, localized swelling, redness, or heat and superficial incision is deliberately opened by surgeon, unless incision is culture-negative); and (4) diagnosis of superficial incisional SSI made by a surgeon or attending physician.

###### Deep Incisional

Infection occurs within 30 days after the operation if no implant is left in place or within 1 year if the implant is in place and the infection appears to be related to the operation and infection involves deep soft tissue (eg, fascia, muscle) of the incision and at least 1 of the following: (1) purulent drainage from the deep incision but not from the organ/space component of the surgical site; (2) a deep incision spontaneously dehisces or is deliberately opened by a surgeon when the patient has at least 1 sign or symptom (fever greater than 38° C, localized pain or tenderness, unless incision is culture-negative); (3) an abscess or other evidence of infection involving the deep incision is found on direct examination, during reoperation, or by histopathologic or radiologic examination; or (4) diagnosis of deep incisional SSI made by a surgeon or attending physician.

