## Introduction

### Background

Surgical site infections (SSIs) are among the most common hospital acquired infections and constitute an important quality criterion in health research [1,2]. The incidence of SSIs in certain indicator procedures is the subject of ongoing surveillance efforts in hospitals and health care systems around the world [1,3,4]. However, SSI rates vary markedly within surgical categories and are poorly represented by routinely monitored indicator procedures such as mastectomy, upper limb amputation, or inguinal hernia surgery [4]. Therefore, relying on indicator procedures to estimate the overall burden of SSIs is imprecise and introduces bias as hospitals may take special precautions to achieve lower SSI rates in indicator procedures. *Staphylococcus aureus* (*S. aureus*) is the most common cause of SSIs, as recently confirmed by a Europe-wide point-prevalence study conducted by the European Centre for Disease Prevention and Control (ECDC) [5].

Treatment of *S. aureus* infections is challenging due to the emergence of multi-drug resistant strains such as methicillin-resistant *S. aureus* (MRSA). To better plan future trials on new treatment strategies, knowledge on incidence and risk factors is of utmost importance.

Currently available data suggest that while the overall SSI rate and the proportion of SSIs caused by *S. aureus* vary, the absolute *S. aureus* SSI rate is similar for different procedures. Focusing on *S. aureus* SSIs, we aim to demonstrate that the *S. aureus* SSI rate is independent of the procedure performed and rather a consequence of cutaneous incisions. Such a demonstration would amount to a paradigm shift and allow future prevention studies to proceed differently.

SSIs are associated with poor outcome, prolonged hospitalization, and increased treatment costs [6]. Estimated excess treatment costs range between US $ 1000 to $20,000 [6-10]. Treatment costs depend, among other factors, on the depth of SSI (superficial, deep, or organ space) and the prior surgical procedure. However, the exact treatment costs remain unknown, as previous estimates are based on limited data from single institutions [9], provider networks [11], or highly aggregated data from surveillance programs [7]. Due to this heterogeneous data source, prior cost estimates for Europe show a wide range of results [12].

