#### Data Collection

##### Cohort

The following variables will be collected from EHRs for descriptive purpose only: (1) age by category; (2) sex; (3) BMI; (4) comorbidities (International Statistical Classification of Diseases and Related Health Problems [ICD-10] codes); (5) diabetes; (6) type of procedure; (7) duration of procedure; (8) occurrence of SSI related to observed procedure within 90 days, including date of diagnosis; (9) wound class.

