### Statistical Analysis

Assuming a mean *S. aureus* SSI rate of 1% [5], incidence rates can be determined with a 95% CI of plus or minus 0.5% by observing 1500 surgical procedures. Therefore, at least 15 centers will be included in the analysis, resulting in 90,000 to 150,000 observed patients. Assuming an incidence rate of *S. aureus* SSI of 1.5% in a population of 150,000, 2250 cases will be matched to 2250 controls.

Data will first be analyzed for missing values. We will perform a qualified evaluation of missingness mechanisms for each variable with more than 1% missing values. In case data are missing completely at random, patients with the missing value will be excluded from that respective analysis step (complete record analysis). For values not missing at random, multiple imputation using chained equations will be performed and compared to a complete record analysis for improved robustness of results. We will perform in-depth descriptive statistics of all parameters observed. Country-based and institution-based incidence rates will be determined for each procedure (eg, ventral hernia repair) and each category (eg, vascular surgery). For each incidence rate, the 95% CIs for a binominal proportion will be calculated. Costs will be calculated for both procedures and categories. Accounting for the usually non-normal distribution of costs in medical settings, statistical analyses (eg, CI construction) will be carried out using non-parametric bootstrap procedures. Reported SSI rates and cost will be further stratified by depth of SSI (eg, superficial, deep). Association between major cost drivers and SSI occurrence, as well as overall costs and SSI occurrence, will be determined using bootstrapped t tests.

Multivariable regression analysis will be used to confirm significance of SSI occurrence for overall treatment costs.

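### Procedure-specific incidences rest on unequal event windows (30 days, or up to 1 year with an implant), so a common 30-day rate is needed before rates are compared across procedures

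*Protocol article*

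**What the plan says.** Under Detection of S. aureus Surgical Site Infection, each identified patient is documented manually and the infection is verified against listed criteria. The windows in those criteria are:

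- Superficial Incisional: "Infection occurs within 30 days after the operation and involves only skin and subcutaneous tissue of the incision". There is no implant distinction.
- Deep Incisional: "within 30 days after the operation if no implant is left in place or within 1 year if the implant is in place".
- Organ Space has the same rule: "Infection occurs within 30 days after the operation if no implant is left in place or within 1 year if the implant is in place".

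Two other places set a different time frame. The Cohort list under Data Collection records "occurrence of SSI related to observed procedure within 90 days, including date of diagnosis", for all patients alike. The detection section says of S. aureus "SSI that occurred in 2016 will be detected using microbiological data", the same calendar year as the operations.

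The Statistical Analysis section gives incidence by country and institution for each procedure and each surgical category: "For each incidence rate, the 95% CIs for a binominal proportion will be calculated". Primary Analysis applies the same approach to the overall and procedure-specific incidence. No common window, time at risk or split by implant status is stated. The Background says the authors aim to demonstrate that the S. aureus "SSI rate is independent of the procedure performed and rather a consequence of cutaneous incisions".

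**The concern.** A proportion of operated patients with an infection is a risk over a stated period. If that period is 30 days for one procedure and up to a year for another, the two proportions are not on the same footing, and the denominator does not show it. This remains true even if every infection is captured, so it is a separate matter from the late infections that the Discussion's Limitations section admits will be missed.

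For a purely descriptive report this would be a labelling matter. Here the article also wants to conclude that the rate is the same whatever the procedure. Unequal windows can mislead in both directions: equal 30-day risks can look different, and a lower 30-day risk in implant surgery can look equal. The overall incidence is also affected, because it blends 30-day and longer risks in proportions set by the share of implant surgery at the participating centres.

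**Working it through.** **The plan's own precision figure.** Sample Size assumes a 1% rate and a 95% CI of ±0.5 points. n = 1.96² × 0.01 × 0.99 / 0.005² = 1521, and the half-width at n = 1500 is 1.96 × √(0.01 × 0.99 / 1500) = 0.504 points. The stated 1500 reproduces to within rounding, so 1% and 1500 per procedure are used below.

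**Contrast of windows.**
- By the infection criteria: 365 / 30 = 12.2-fold.
- If the 90-day field caps the criteria: 90 / 30 = 3-fold.
- If 90 days replaced the criteria for all procedures: no contrast. The article does not say this.

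**Effect on the reported rate.** Let f be the share of countable implant infections that arise after day 30. The article gives no timing, so f is an assumed range. With a 30-day risk of 1% in both procedures, the implant procedure reads p = 1% / (1 − f). The rejection probability is for a two-sided 5% normal comparison of p with 1%, using 1500 operations in each procedure:

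| f | p | gap, points | probability of rejection |
|---|---|---|---|
| 10% | 1.11% | 0.11 | 6% |
| 20% | 1.25% | 0.25 | 10% |
| 30% | 1.43% | 0.43 | 19% |
| 40% | 1.67% | 0.67 | 36% |
| 50% | 2.00% | 1.00 | 62% |

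For f = 50%: SE = √[(0.01 × 0.99 + 0.02 × 0.98) / 1500] = 0.00443, and Φ(0.0100 / 0.00443 − 1.96) = 0.62. For f = 10%: SE = 0.00373, and the two tails sum to 0.048 + 0.012 = 0.06, close to the nominal 5%.

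In the other direction, an implant procedure with a 30-day risk of 0.5% and f = 50% would read 0.5% / 0.5 = 1.0%, the same as a non-implant procedure with twice its 30-day risk.

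**What limits f.** Only deep and organ/space infections can count late. If a share s of the countable implant infections is superficial, the late share among the others must be f / (1 − s). With s = 50% (assumed), f = 50% would need all of them to arise after day 30. With s = 30%, it would need 71%. The upper rows of the range are therefore demanding.

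**What the 2016 limit does.** Assume operations are spread evenly over the 366 days and detection stops at year end. The mean observable share of a window of w days is 1 − w / (2 × 366), and the share of operations with a full window is (366 − w) / 366.
- w = 30: 96% of the window on average; full for 92% of operations.
- w = 365: 50% on average; full for 0.3% of operations.

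The limit therefore narrows the contrast but does not equalise the windows.

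**The case against.** The strongest reply is that the window is part of the case definition. The implant-dependent windows come with the surveillance criteria the study adopts, and a binomial proportion validly estimates the risk of an infection so defined. That stands: neither the definition nor the estimator is wrong in itself.

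It is also true that no test between procedures is planned. The objectives are to determine incidences, and the independence claim appears only in the Background. The rejection probabilities above illustrate scale and are not error rates of a planned analysis. Even so, the claim is a stated aim of the article, and the per-procedure proportions are the natural evidence for it.

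A reader might infer a 12-fold difference in exposure, or a near-certain false finding: with 5000 operations per procedure the same comparison at f = 50% would reject 98% of the time. The article supports neither. It does not use 5000 per procedure. The 90-day field, the 2016 limit and in-patient-only laboratory data all shorten the realised implant window, and superficial infections are unaffected.

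The 90-day field might be read as one window for everyone. That would remove the contrast, but nothing says it overrides the criteria used to verify each case.

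Stratification by depth helps only in part. The superficial stratum shares one window, but within the deep stratum the window still depends on the implant. Poisson regression is named only as an example of a sensitivity analysis, without a time offset. Detailed tables can be left to the analysis plan, but the article itself fixes the event definition, the estimator and the intended conclusion, and these do not fit together.

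**Conclusion.** The point holds in a limited form. As written, the plan places proportions with different windows side by side and pools them, while aiming to conclude that the rate is unrelated to the procedure. For deep and organ/space infections, a difference or an apparent equality between procedures can come from the window alone.

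The size cannot be derived from the article, because it depends on the timing of implant infections. The gap is 0.11 to 1.00 percentage points on a 1% rate over the assumed range for f, before any narrowing by the 90-day field, the 2016 limit or in-patient detection. At the low end it is negligible. At the high end it is twice the planned half-width of 0.5 points.

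A reader might conclude that the primary incidence is invalid and should be replaced by a 30-day rate. The article does not support that. The definition-based rate is a legitimate quantity, and replacing it would change what the study estimates. The need is for an additional rate on a common window and a clear statement of which window applies. This should be corrected, but it does not undermine the study.

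**What to change.** In Statistical Analysis and Primary Analysis:

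1. Keep the incidence based on the infection criteria and label each rate with its window.
2. Add the cumulative incidence of S. aureus SSI within 30 days of surgery for every procedure, for every category and overall, computed from the recorded date of diagnosis.
3. Base any statement that the rate is independent of the procedure on this common-window rate only.
4. Reconcile the Cohort list (90 days), the detection section (infections in 2016) and the Deep Incisional and Organ Space criteria (30 days or 1 year), and state which window defines the primary numerator. If detection does end with 2016, say how operations in the last 30 days of the year enter the 30-day rate; they are about 8% of the total if operations are spread evenly.

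The cost is analysis wording and one extra table. The date of diagnosis is already in the Cohort list. Implant status, which is not listed there, is not needed for the 30-day rate. The drawback is that the common-window rate leaves out later implant infections, but these remain in the definition-based rate.
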